### Primary outcome measure

The primary outcome of this trial is pain intensity after acute dressing application (*see* Measure 2 in Fig. 3). Observational reports from nursing staff using the FLACC scale will be used to measure this primary study outcome for all participants enrolled in this trial.

**Fig. 3 Fig3:**
[figure not shown]
Acute pain assessment in the Department of Emergency. Following cold running water first aid, pain will be assessed before and after the application of the randomised dressing, peak pain scores during wound cleaning and debridement, and before and after silver dressing application. Pain scores will be collected from the patient (where appropriate), observational pain scores will be collected from parents and caregivers, and Face, Legs, Activity, Cry, Consolability scale scores will be collected from nursing staff

#### Ancillary pain measures

Pain intensity will be assessed before and after hydrogel dressing application and before and after silver dressing application, using self-report scales, parental/carer-specific, and nursing-specific pain scales (*see* Fig. 3). The set points of data collection will be recorded on a data collection form for patient and external observers to communicate pain intensity in a more accurate manner. The three physiological and psychological age-specific scales outlined below have been selected to allow assessment of pain and distress.The FPS–R will be used to assess pain in children aged 4 years and older. The FPS–R is a self-rated, self-administered scale that uses images of facial expressions to assess pain intensity in children [41, 42]. The FPS–R has been shown to be superior to other faces scales [43] and has been validated in the literature as having a strong positive correlation (*r* = 0.93) with the visual analogue scale for pain (VAS-P) in children aged between 5 and 12 years [44]. Authors of a systematic review of self-report pain intensity measures for use in paediatric clinical trials reported that the FPS–R appears to be the most psychometrically sound pain assessment tool for children aged between 4 and 12 years [42]. Furthermore, a 2010 systematic review of the FPS–R for child self-reporting of pain intensity concluded that the FPS–R is recommended as a research tool because of the measure’s utility and psychometric features [45].The FLACC scale [46] will be used by nursing staff to assess pain and distress levels. The FLACC is an observational behavioural scale that has been validated for pain assessment in children aged between 2 months – 7 years [46]. Observational pain scales such as the FLACC are widely used in paediatric clinical research [47]. A prospective observational investigation conducted in 2012 assessed the use of the FLACC scale to measure pain and distress in patients aged between 6 and 42 months (*N* = 125). This study found that FLACC scores can be high during non-painful procedures, as well as during the restraining phase of procedures [47]. These findings further support the notion that the FLACC assesses a composite of pain and distress in young children.VAS-P for children aged 8 years and older and visual analogue scale observer (VASobs) for parent/guardian reports will be used. These scales have been chosen because they are age-specific and reliable and have been validated in recent literature. VASs have been validated and frequently used to measure pain in adult populations and in paediatric populations as young as 5 years of age [48–50]. When quantifying pain intensity in pre-verbal and early-verbal children, who are unable to self-report, the VASobs repeatedly appears in the literature as a proxy for self-reports of pain [50–52]. Earlier studies have demonstrated that young burn patients can readily grasp the concept of quantifying their pain using anchored scales and even in moments of extreme discomfort are able to continue giving pain scores [53].

Physical measures of pain and distress will also be recorded at each of the measurement points depicted in Figs. 3 and 4. These measures include pulse rate, respiratory rate and temperature because increases in these physiological measures have been shown to be indicative of pain and distress.

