**Methods/design:**

A randomised controlled trial will be conducted to assess the effectiveness of Burnaid® as an analgesic adjunct to cold running water first aid for the treatment of paediatric burns. Participants will include children aged between 0 and 16 years with an acute thermal burn injury (total burn surface area < 20%) presenting to the Department of Emergency within 24 h of the burn occurring. Participants will be randomised into one of two groups: (1) Burnaid® hydrogel (intervention arm) or (2) plastic wrap (control arm). Participants will also be stratified into one of two groups based on factors that influence pain intensity: (1) high pain risk or (2) low pain risk. High pain risk factors include foot burns, hot coal/ash/fire pit burns, burn area greater than 5%, and circumferential burns. The primary outcome is the intervention’s effect on reducing acute pain. Secondary outcomes include days to re-epithelialisation, pulse rate, temperature, salivary cortisol and α-amylase, anxiety, and cost-effectiveness. Sample size calculations have shown that 36 participants will be recruited into each group.

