### Use of hydrogels on burns

Current guidelines recommend burn wound covering after CRW first aid [8]. Acute burn wound coverings are required to be transparent and non-adherent and to have high application and removal ease. Plastic wrap fulfils these criteria and, excluding applications to the face, is a practical choice of dressing for acute burn injuries. In comparison to plastic wrap, Burnaid® hydrogel dressings (Mundicare, Sydney, Australia) may provide additional pain relief via an evaporative cooling effect and may thereby assist in wound healing [23–25]; however, empirical evidence is still limited. The Burnaid® hydrogel dressing comprises a 3-mm-thick, sterile, open foam polyester urethane pad that is impregnated with a propylene glycol gel which contains more than 90% purified water. Following the recognised standard of first aid treatment for acute burn injuries, Burnaid® is recognised as an adjunct to first aid whose aim is to reduce pain. Moist interactive wound dressings provide pain relief via an evaporative cooling effect and create a moist environment which soothes exposed nerve endings in the skin [26]. Hydrogel dressings provide a concomitant cooling and wound-covering function and dissipate heat from the burn wound, and dressings come in a wide range of sizes which can be applied to all areas of the body [23, 27, 28].

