**Fig. 2 Fig2:**
[figure not shown]
SPIRIT figure. SPIRIT schedule of study recruitment, intervention and assessments. Allocation to the intervention group will occur in the Department of Emergency at Lady Cilento Children’s Hospital upon patient admission following a thermal burn injury; t1 = 3–5 days after burn injury and each subsequent dressing change; t2 = 3 months after burn injury; t3 = 6 months after burn injury

Following patient enrolment and randomisation, acute measures will be collected in LCCH DEM. Acute measures will include pain (measured using the Faces Pain Scale–Revised [FPS-R]; Face, Legs, Activity, Cry, Consolability scale [FLACC]; and visual analogue scale [VAS]), pulse rate, temperature, respiratory rate, and salivary cortisol and α-amylase, which will be recorded by the primary investigator. Acute measures will be collected before and after the application of the randomised dressing and before and after silver dressing application from the child, parent/guardian, and nursing staff. In addition, peak FLACC scores during wound cleaning and debridement will be documented, as will all analgesia and distraction techniques. All participants will have their burn wounds photographed using 3D imaging after wound debridement in the DEM to assess burn area. Patients (where appropriate) and parents/caregivers will be sent home with a diary to record pain scores and medications required prior to their first change of dressing (COD), which will typically occur 3 days after injury. Participants and parents/caregivers will be asked to bring this home diary with them to their first dressing change in the burns OPD.

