#### Adverse effects

The proposed intervention is considered to be part of standard pre-hospital care and is currently used by Queensland Ambulance Services, despite Burnaid® products not being used at the LCCH DEM and burns OPD. Therefore, minimal adverse events are expected. Known potential adverse events (such as hypothermia, infection, haematoma, excessive exudates, unpleasant sensations, allergic reactions, chondritis, and disruption of the skin on dressing removal) have a standardised management protocol at LCCH DEM and burns OPD. In addition, children with known adverse reactions to hydrogels will be excluded from the trial. Adverse effects of the hydrogel dressing will be monitored by reviewing patient medical records and via self-report data from parents/caregivers, participants (where appropriate), and treating clinicians. All adverse events will be reported to the clinical health service and the overseeing HREC. If a consultant believes that Burnaid® hydrogel dressings were not appropriate for a patient’s treatment, discontinuation or alteration of treatment will be at their discretion, and data collection for such participants will cease from that time point.

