## Discussion

Pain and distress following first aid remains a major challenge when treating acute paediatric burn injuries, and literature shows that increased pain and stress can have maladaptive effects on wound healing [35, 37, 67] and patient outcomes [68]. Although Burnaid® hydrogel dressings are frequently being used by Queensland Ambulance Services during patient transport to hospital for burn injuries [18], a limited number of high-level studies have been conducted examining the clinical utility of these dressings, particularly in relation to analgesic properties and wound-healing effects. The widespread use of hydrogel burn dressings (such as Burnaid®, BurnShield®, and Water-Jel®) is alarming owing to the lack of research supporting their use as a first aid dressing [69]. This randomised controlled trial will provide high-level evidence to determine if Burnaid® hydrogel dressing provides superior pain relief in comparison to plastic wrap as an acute burn wound covering applied after first aid in paediatric patients with thermal burn injuries. Establishing which dressing is more effective in reducing acute pain is critical to clinical care and also to facilitate further evidence-based guidelines in this field.

Burns are a painful and traumatic experience, particularly in children. Considering the adverse psychological and physiological effects secondary to pain, optimal pain management should be viewed as an essential and requisite component in acute paediatric burn treatment [9]. Reduced pain and anxiety positively influences re-epithelialisation rates [3], and time to re-epithelialisation is a good predictor of scar outcome in patients with burn injuries [70]. This further validates attempts to speed up re-epithelialisation rates. Even if hydrogel products are more expensive than current standard acute wound coverings, the cost of treating adverse scarring is substantial in resources and time, as well as in cosmetic outcome for the patient. Burnaid® hydrogel dressings have been shown to be effective evaporative cooling agents, which is why these dressings are hypothesised to have an analgesic effect during acute burn care [69].

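### Around the randomised dressing, temperature cannot serve as a pain and distress outcome, because the dressing under test is said to work by cooling

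*Protocol article*

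**What the plan says.** Under Ancillary pain measures, temperature is grouped with pulse and respiratory rate: "Physical measures of pain and distress will also be recorded at each of the measurement points depicted in Figs. 3 and 4". The reason given is that these are "pulse rate, respiratory rate and temperature because increases in these physiological measures have been shown to be indicative of pain and distress". The abstract makes temperature an outcome in its own right: "Secondary outcomes include days to re-epithelialisation, pulse rate, temperature, salivary cortisol and α-amylase, anxiety, and cost-effectiveness".

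Data collection fixes the timing in the acute phase: "Acute measures will be collected before and after the application of the randomised dressing and before and after silver dressing application". Temperature is taken again at each later dressing change in the outpatient department.

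On how the intervention works, Use of hydrogels on burns says that Burnaid, compared with plastic wrap, "may provide additional pain relief via an evaporative cooling effect and may thereby assist in wound healing". Of the dressing class it says: "Hydrogel dressings provide a concomitant cooling and wound-covering function and dissipate heat from the burn wound". The Discussion repeats the point: "Burnaid® hydrogel dressings have been shown to be effective evaporative cooling agents".

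On harm, Adverse effects begins its list with "Known potential adverse events (such as hypothermia, infection, haematoma", and First aid gives prevention of hypothermia as one reason for covering the burn.

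**The concern.** A physiological marker of pain is useful only if treatment moves it through pain. By the protocol's own account, the hydrogel acts on heat. If a rise in temperature signals pain, the natural reading of a lower value on Burnaid is less pain, yet a cooling dressing could produce that value with pain unchanged. A large enough fall is also what the safety section calls an adverse event.

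The setting makes this matter. The primary outcome is a FLACC score given by nurses who know the allocation (Primary outcome measure; Blinding). Readers may look to instrument readings for corroboration that does not depend on an observer's judgement. Temperature looks like such a reading, but around the randomised dressing it has a direct route to treatment that bypasses pain. The protocol states no such route for pulse, respiratory rate, cortisol or α-amylase.

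**Working it through.** **1. Which readings are exposed**

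| Reading | Could direct cooling from the randomised dressing affect it? |
|---|---|
| Before the randomised dressing | No; it precedes the dressing |
| After the randomised dressing (on for at least 20 min) | Yes |
| Before and after the silver dressing, same attendance | Possibly, until the cooling has passed |
| Later dressing changes (the first typically 3 days after injury) | No; the hydrogel is long removed |

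The problem is therefore confined to the first attendance.

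**2. What the comparison estimates.** The between-arm temperature difference after the dressing is the sum of (a) any change that comes through less pain and distress and (b) any direct cooling. The documents give no information that would separate (a) from (b). Adjusting for the pre-dressing reading removes chance imbalance between arms, but not (b), which arises after randomisation.

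**3. The plan's own figure.** Sample size uses an SD of 2.4 and a difference of 1.8 in pain score, so d = 1.8/2.4 = 0.75. A two-sample t test at 0.05 (taken as two-sided; the protocol does not say) with 80% power needs 28.9, that is 29 per arm, as stated. The target of 72 is 36 per arm. None of this depends on temperature.

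**4. Illustration for temperature.** The documents give neither a temperature SD nor an expected shift, so both are assumed. Let the dressing lower temperature by d SDs with no effect on pain. The noncentrality is d × √(n/2), referred to a t distribution with 2n − 2 degrees of freedom. For d = 0.67 and n = 36 it is 0.67 × √18 = 2.84, against a critical value of 1.99 on 70 degrees of freedom.

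| Assumed direct fall (SD) | P(significant), 29 per arm | P(significant), 36 per arm |
|---|---|---|
| 0.25 | 0.16 | 0.18 |
| 0.47 | 0.42 | 0.50 |
| 0.50 | 0.47 | 0.55 |
| 0.67 | 0.71 | 0.80 |
| 0.75 | 0.80 | 0.88 |
| 1.00 | 0.96 | 0.99 |

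The fall that gives 80% at 36 per arm is 0.6696 SD. For assumed SDs of 0.4, 0.5 and 0.7 °C that is 0.27, 0.33 and 0.47 °C. The table shows what a shift would do if it occurred. It is no evidence that a shift of any given size will occur.

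**The case against.** Several points on the other side stand, and each limits a stronger reading that a reader might draw.

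- **That the trial will score a fall as benefit.** The article does not say so. It says that increases indicate pain and distress, and the abstract lists temperature without a direction. The favourable reading of a fall follows naturally from the stated rationale, but it is an inference.
- **That the outcome is certainly biased towards Burnaid.** The text speaks of heat leaving the wound, whereas temperature is listed beside the vital signs. The measurement site is not given, which a condensed article may leave to the full protocol. Burns are under 20% of body surface, and cold running water precedes the dressing in both arms. The effect on a recorded temperature may be small. That hypothermia is a listed adverse event makes an effect credible, not certain.
- **That a safety signal is hidden.** It is not. Temperature is a reported outcome, Data analysis promises descriptive statistics for all outcomes, and hypothermia has its own adverse-event route through medical records and reports from families and clinicians. A variable can be both an outcome and safety data, so the two sections do not contradict each other.
- **That temperature should go as a distress measure throughout.** Direct cooling cannot reach readings taken days after the hydrogel came off.

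It is also fair to say that any variable would reach significance under an assumed shift, so the table cannot support severity. Nor does the main conclusion of the trial rest on temperature. What these points leave untouched is the interpretation: in the acute comparison, a temperature difference cannot be attributed to pain. If cooling is how the dressing relieves pain, a fall shows that cooling was delivered, and the relief still has to be shown on the pain scales.

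**Conclusion.** The concern holds for the acute readings. The protocol names temperature as a secondary outcome and classes it as a marker of pain and distress, while describing an intervention whose proposed difference from control is cooling and listing hypothermia as a harm. After the randomised dressing, a lower temperature on Burnaid could reflect direct cooling or harm and not less pain.

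The size of the bias is unknown and may be small. The figures above rest on an assumed shift, an assumed SD, a two-sided 0.05 test and an unadjusted comparison. The point concerns how one secondary outcome is interpreted. The FLACC primary outcome and the sample size are not affected. Because the correction costs little and the flaw lies in a stated classification, it should be made.

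**What to change.** Under Ancillary pain measures and in the list of secondary outcomes, state that temperature around the randomised dressing in the emergency department, and until any cooling from that dressing has passed, will not be interpreted as a pain or distress outcome. Report it by arm as a direct-effect and safety variable: change from the pre-dressing reading, and the lowest value, with the measurement site stated. Keep pulse, respiratory rate and the salivary markers as the acute physiological distress measures. Temperature at later dressing changes may stay as planned.

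The cost is wording only, since the same readings are taken at the same times. The downside is one fewer acute efficacy secondary outcome.

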**Fig. 4 Fig4:**
[figure not shown]
Pain assessment during change of dressing follow-up appointments. All participants will have their pain assessed in the waiting room of the Pegg Leditschke Children’s Burns Centre Outpatient Department prior to premedication for their follow-up dressing changes. Pain scores will also be measured subsequent to silver dressing removal, prior to the application of new silver dressings, and after application of the new silver dressing

### Secondary outcome measures

#### Days to re-epithelialisation

The number of days from the date of the initial burn until 95% wound re-epithelialisation occurs, the surface area of the affected area, and the percentage of wound re-epithelialisation will be calculated using three methods: (1) clinical judgment of the treating consultant, (2) 3D photography (3D LifeViz™ System; QuantifiCare, Valbonne, France) and analysis using specialist computer software, and (3) blinded review of the 3D photographs by a panel of burn specialists. The 3D LifeViz™ System will be used to photograph all burns upon first presentation to the hospital following wound debridement and at each subsequent burns OPD visit for dressing changes and wound care. This will be performed for all participants until burn wounds are deemed to be 95% re-epithelialised or are grafted. Research has found 3D photography to be a valid and reliable measure of acute burn wound surface area in an Australian paediatric population [54, 55]. In order to ensure accurate measurement calibration in the associated DermaPix™ software package (QuantifiCare), a ruler will also be included in all 3D photographs. The 3D images will be analysed by the primary investigator using the DermaPix software programme to determine the surface area of the burn and the area of re-epithelialisation of the wound at each COD. A panel of burn specialists, which will be composed of consultants and nursing staff, will perform a blinded review of the 3D images and will assess the level of re-epithelialisation and appearance of each participant’s burn, mapping out the edges of the wound and all unhealed areas. We will further examine concordance between the burn specialist’s clinical assessment and the DermaPix mapping programme regarding re-epithelialisation.

#### Staff and caregiver perspectives on dressings

Perception of ease of dressing application, removal, flexibility, and conformity will be rated by medical and nursing staff using a self-reported 0–10 Numeric Rating Scale (NRS) for both the Burnaid® hydrogel dressing and plastic wrap groups. Clinical staff will also be surveyed again using the same NRS after recruitment has ceased in order to examine any changes in their perception of either acute wound covering. In addition, parent/caregiver and patient (when appropriate) perception of comfort, ease of movement, and ease of dressing application/removal will be measured using an NRS. It is noted that ease of dressing measurements in the DEM will be confounded owing to lack of blinding and as a result of the variable nature, size, and anatomical location of the areas to be dressed.

#### Scar/skin condition at 3 and 6 months

At 3 and 6 months after the date of injury, a face-to-face follow-up will be performed with all participants (intervention and standard care groups) to assess the skin and scar characteristics of the affected area. This assessment will involve (1) 3D camera imaging (3D LifeViz™ System), which will be used to determine scar area and volume above the skin; (2) ultrasound scanning (BT12 Venue 40 MSK; GE Healthcare, Chicago, IL, USA), which will be used to measure the height of the scar; and (3) the POSAS measurement tool, which will be used to assess scar severity. The POSAS will be completed with the patient (if aged 6 years or older) and the parent/caregiver, and it will document observer scale items of scar thickness, vascularity, pliability, pigmentation and relief in addition to patient scale items of itch, pain, colour, stiffness, thickness and irregularity. In addition, DSM II Skin ColorMeter analysis will be performed to assess the lightness, redness or erythema, and pigmentation of the scar. The DSM II ColorMeter is an objective tool that uses tri-stimulus reflectance colourimetry and narrow-band photometry to assess scar characteristics, and it has been demonstrated to have inter-observer reliability intra-class correlation coefficients of 0.94 for lightness, 0.94 for erythema and 0.83 for pigmentation in scar assessment [56].

